## Potential Benefits

The conduct of this randomised controlled trial will be important to prove the effectiveness of a pharmacist-led educational protocol. If this protocol is shown to be effective in improving clinical outcomes and participant quality of life, the organisation will have clearer guidance for pharmacists in providing counselling points to patients with allergic rhinitis. Should this protocol be implemented in clinical practice, the "education" section of this protocol can be used as a standard communication tool such that all of the healthcare providers, including the doctor, give the same advice to the patients. This would address the common problems faced by patients who complain of receiving fragmented and conflicting information from different healthcare providers (Cvetkovski et al., 2020).

Patients who receive adequate information about the nature of the disease, pharmaceutical treatment, and treatment expectations change their behaviour in disease management and medication adherence (Lourenço et al., 2020). This would potentially improve their symptom control and quality of life. This in turn will reduce the healthcare burden in terms of clinic visits, cost, and comorbidities.

## 3 OBJECTIVES

### Primary Objective

To determine the effectiveness of the pharmacist-led educational protocol in managing allergic rhinitis between a control group of patients who are receiving standard pharmaceutical care and an interventional group of patients receiving an educational interventional protocol plus standard pharmaceutical care, based on the following specific parameters: -

1. Knowledge of intranasal corticosteroids
2. Symptom control
3. Medication adherence
4. Quality of life

### Secondary Objective

To determine within group difference for the 4 primary parameters (knowledge, symptom control, medication adherence, quality of life)

**Societal value or beneficial outcome of study**

Should the pharmacist-led protocol proven to be effective in improving knowledge, symptom control, medication adherence and quality of life in allergic rhinitis patients, this protocol is potentially implemented in clinical practice, which in turn would reduce the burden of the ENT outpatient clinic, as well as reduce the healthcare setting burden.

**4 ETHICS & REGULATORY CONSIDERATIONS**

**Ethical conduct of the study**

Ethical approval will be obtained from the Medical Research and Ethics Committee (MREC) through NMRR before the study is conducted.

The study will be conducted in compliance with the protocol and standard operating procedures. These are designed to ensure adherence to the ethical principles that have their origin in the "World Medical Association Declaration of Helsinki", "Malaysian Guidelines for Good Clinical Practice" and applicable regulatory Requirements.

All study data will be stored for 3 years after the study findings are published and then destroyed. All data will be kept under lock and key in the office cabinet and only accessible by the researchers. Participants in this study will not be given access nor informed of the findings' outcome. The participants will be informed with the new information if it becomes available during the study. The patient educational material will be shared with all the participants, including the control group, at the end of the study.

Participants can choose to withdraw at any time. The physician or investigator may withdraw participants if there is an associated risk with the participants' continuing participation in this study. All withdrawn participants will be reminded to continue receiving their standard medical care at the ENT clinic at Hospital Raja Permaisuri Bainun. Withdrawn participants will not be replaced. The data collected from the withdrawn participants will be included in the analysis.

The participants will not be informed individually about the study findings; however, the patient education material will be shared with all the participant (including the control group)

at the end of this study. The control group participants will be subjected to structured pharmacist counselling at the end of study, right after their data are collected. All the information obtained from this study will be kept confidential and only summarized data, without unique identifier, will be presented in reports or publications upon getting permission from the Director General of Health, Ministry of Health Malaysia.

## **Informed consent and subject information**

Written informed consent will be obtained from every participant prior to participation in this study. The investigator will inform every participant in detail about the nature of the study, its purpose, and the probability of random assignment to intervention groups, those aspects of the study that are experimental, the procedures involved, the reasonably expected benefits, the expected duration of participation will be 6 months and the approximate number of 154 participants will be involved.

A copy of the Patient Information Sheet and signed Consent Form will be given to the participants (Appendix A). The original copy will be filed by the principal investigator in the Investigator's Study File.

The participants will be informed that

- Their participation in this study is voluntary and that they may withdraw from this study at any time for any reason and that withdrawal of consent will not affect their subsequent medical treatment or relationship with the treating physician.
- They will be notified in a timely manner if information becomes available that may be relevant to their willingness to continue participation in the study.
- The risk of participating in this study is minimal, should any injuries occurred; they will be advised to come to the ENT clinic or emergency department immediately. Tentatively, no additional cost is anticipated to be incurred to the patients.
- This study does not receive any external funding; the participants will not be paid.
- Any foreseeable circumstances and/or reasons by the discretion of the physician under which the participants' participation in the study may be terminated.
- The principle investigator to contact for further information regarding the study and whom to contact in the event of study related injury.

The place to obtain written informed consent will be conducted at a designated meeting room that is empty during clinic day and it is considered sufficiently private for the participants and investigator, which is located in the ENT outpatient clinic. The timing to take written informed consent is set right after patients have attended their routine visit to seek medical consultation with the medical doctor.

## **Patient protection procedures**

### **Procedures in the event of Emergency**

In the event of emergency, the participants are advised to go to the emergency department, Hospital Raja Permaisuri Bainun or to their nearest emergency department of any government-funded hospitals.

If participants' allergic rhinitis symptoms are not adequately controlled, they are advised to walk-in to the ENT clinic without having to wait for the appointment date.

### **Procedures in the event of Pregnancy**

The patients will be instructed to inform the investigators and physician if she becomes pregnant during the study. Should the participants become pregnant, she will be discontinued from the study. Since there is no investigational product involved, the participants will not be followed up thereafter.

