### Study design

This study will be conducted at the Hospital Raja Permaisuri Bainun in the state of Perak, Malaysia. A pharmacist-led educational protocol that has been validated by the researchers in other study will be adapted as an interventional tool for this study. This pharmacist led-protocol consists of patient education material and structured pharmacist counselling.

This trial is a single-centre, randomised, two-arm, and parallel-group controlled trial that will be conducted to determine the effectiveness of the pharmacist-led educational protocol. Adult patients diagnosed with moderate to severe AR who attend an outpatient ENT (ear, nose and throat) clinic in Hospital Raja Permaisuri Bainun will be recruited and randomly allocated at a 1:1 ratio into control and intervention groups.

The control arm will receive the current standard of pharmaceutical care, i.e., it is a health service that patient obtaining their medication from the outpatient pharmacy following a session of medical consultation at the ENT clinic, whereas the intervention arm receives the educational material and pharmacist counselling plus standard pharmaceutical care.

Baseline data will be collected and both groups will be followed up post-randomization on Day  $60 \pm 7$ , Day  $120 \pm 7$  and Day  $180 \pm 7$ . Participants will be contacted virtually (Zoom, Google Meet, or Whatapps call, or telephone call) or face-to-face, depending on the feasibility and standard operating procedures of the outpatient ENT (ear, nose, and throat) clinic at Hospital Raja Permaisuri Bainun during the follow-up on Day  $60 \pm 7$  and Day  $120 \pm 7$ . Meanwhile, the end-of-study follow up will be done at the routine scheduled clinic visit, which is around Day  $180 \pm 7$ .

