## **Statistical analysis**

An intention-to-treat analysis will be used to include all of the patients who were assigned to each group after randomization. The data analysis will be done using SPSS version 20.0. Descriptive data will be expressed as mean and standard deviation (SD) if the data is normally distributed, or median and interquartile range (IQR) if the data is not normally distributed. Categorical data will be presented in frequency and percentage.

To determine the knowledge level, The “yes” answer will be given a score of two, the “no” answer will be given a zero score, and “not sure” will be given a score of one (Retinasekharan et al., 2021). The outcome will be presented in mean score and standard deviation for each group. Each question will be analysed separately. The knowledge levels will be assessed at baseline, Day 120 $\pm$ 7 and on Day 180  $\pm$ 7. Between-group comparisons will be analysed using Two-way repeated measure ANOVA to compare mean score different between two groups. Meanwhile, the two-way repeated measures ANOVA will show the findings for the within-group comparison. A P-value of < 0.05 will be considered statistically significant.

The Total Nasal Symptom Score (TNSS) is the sum of scores for each of nasal congestion, sneezing, nasal itching, and rhinorrhoea at each time point, using a four-point scale (0–3), where 0 indicates no symptoms, a score of 1 for mild symptoms that are easily tolerated, a

score of 2 for awareness of symptoms that are bothersome but tolerable, and a score of 3 is reserved for severe symptoms that are hard to tolerate and interfere with daily activity. A higher score indicates the more severe the symptoms are, and the main outcome of TNSS will be generated as a mean and standard deviation. A mean score will be calculated separately for the past 12 hours and past 2 week. A two-way repeated measure ANOVA analysis will be employed to determine the mean difference between the scores of the control group and the interventional group in order to determine the overall effectiveness of the intervention. Within-group comparisons will be shown as part of the outcome of the two-way repeated measures ANOVA. A value of  $P < 0.05$  is considered statistically.

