### **Participant withdrawal & drop-out**

The participants are free to withdraw from the study at any time for any reason. For safety reasons, the participants may also be withdrawn from the study at any time at the discretion of the investigator. Reasons for withdrawal will be documented. The participant who withdrew will not be replaced. In the event of pregnancy, the patients will be instructed to inform the investigators and physician if she becomes pregnant during the study. Should the

913 participants become pregnant, she will be discontinued from the study. Since there is no  
914 investigational product is involved, the participants will not be follow up thereafter.

915 **Permitted and not permitted medications / treatments during trial**

916 This study did not involve any new investigational products or new invasive procedures or  
917 devices. Participants in the intervention will be exposed to educational materials and  
918 structured pharmacist counselling. Participants in both groups will continue to receive the  
919 usual care at the ENT outpatient clinic and pharmaceutical service at the outpatient  
920 pharmacy. There is no issue pertaining to the permitted or not permitted  
921 medications/treatments during this study. Participants are allowed to take all the prescribed  
922 medications; the over the counter medication consists of medication of interest  
923 (Antihistamine, Corticosteroids, Anticholinergics, Leukotriene receptor antagonists, Nasal  
924 saline, Decongestants, Beta- blocker) aimed to treat symptoms of allergic rhinitis that the  
925 participant purchased outside will be recorded.

926

927 There is no conclusive evidence to prove the use of traditional and complementary products  
928 improves allergic rhinitis significantly. The participants are allowed to take their traditional  
929 and complementary products as per their own routine.

930 **Rescue medication / procedure.**

931 The intervention group is receiving education materials as well as structured pharmacist  
932 counselling, and hence the risk of being exposed to unforeseeable risk is minimal. Should  
933 the participants have a flare-up of allergic rhinitis symptoms, they are advised to seek  
934 medical attention from the ENT outpatient clinic without waiting for their scheduled clinic  
935 appointment. If the patient's allergic rhinitis co-exists with asthma, they will be advised to go  

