**Lost to follow up**

Subject will be considered lost to follow up if they failed to be contacted without stating to withdraw consent. The researchers must attempt to contact the subject (3 phone calls per day for 3 consecutive days and if necessary, a letter to the subject's last known mailing address) before being considered as lost to follow up. These contact attempts should be documented in the subject file.

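### Pregnancy ends all study follow-up for a reason that does not require it, and the plan never separates stopping the counselling from stopping outcome collection

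*Combined protocol and SAP*

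**What the plan says.** **Pregnancy.** Under Procedures in the event of Pregnancy (section 4): "Should the participants become pregnant, she will be discontinued from the study". The next sentence reads: "Since there is no investigational product involved, the participants will not be followed up thereafter". The section Participant withdrawal & drop-out repeats both statements.

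**Withdrawal by the study team.** Participant withdrawal & drop-out states: "For safety reasons, the participants may also be withdrawn from the study at any time at the discretion of the investigator". Ethical conduct of the study has a similar rule: "The physician or investigator may withdraw participants if there is an associated risk with the participants' continuing participation in this study". Neither says whether questionnaires continue afterwards. The ethics section adds that withdrawn participants are not replaced, that they are reminded to continue standard care at the ENT clinic, and that the data collected from them enter the analysis.

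**Loss of contact.** Under Lost to follow up, the status applies after "3 phone calls per day for 3 consecutive days and if necessary, a letter". Study design says that "the end-of-study follow up will be done at the routine scheduled clinic visit", at around Day 180, with each time point allowed plus or minus 7 days.

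**Analysis.** Statistical analysis states: "An intention-to-treat analysis will be used to include all of the patients who were assigned to each group after randomization". The method for all four primary parameters is a two-way repeated-measures ANOVA. No rule for missing visits is given.

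**The concern.** Stopping an intervention and stopping measurement are different decisions, and this plan treats them as one. An analysis of all randomised patients needs outcomes from people whose counselling has stopped as well as from those who continue. The pregnancy rule ends measurement in someone who can be reached and may be willing to go on, and the reason offered concerns product exposure, which has no bearing on a questionnaire. It also ends the study's recording of medication side effects (Assessment of safety, Appendix D), in a trial where adherence to a nasal steroid is a primary parameter.

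The withdrawal rules leave the same question open. Withdrawal from the study is naturally read as the end of all assessments, and nothing provides for another course. The loss-to-follow-up rule does not say what happens at the next scheduled visit. That matters for participants without a smartphone, who bring diary cards and home-completed EQ-5D-5L forms to the Day 180 visit. If contact stopped earlier, forms already filled in might never be collected.

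At stake are avoidable missing outcomes in a plan with no rule for handling them.

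**Working it through.** **1. The rules side by side**

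| Route out | Does the text end outcome collection? | What is kept |
|---|---|---|
| Pregnancy | Yes, expressly, in two sections | Data already collected |
| Withdrawal for safety or risk | Not stated; implied by withdrawal from the study | Data already collected |
| Loss to follow-up | No; it classifies people who cannot be reached | Not addressed |

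Only the first row is an explicit instruction to stop. The second is an ambiguity and the third a gap about later visits.

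**2. Does keeping collected data solve the problem?** Only in part. It does not supply the later outcomes. In addition, a repeated-measures ANOVA as normally run uses only participants with every visit. A woman who became pregnant after Day 120 would then also lose her Day 0, 60 and 120 values from the analysis, although the ethics section says they are included.

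**3. The plan's own sample size.** The largest between-group requirement is for EQ-5D-5L utility: f = 0.1885976, m = 4 measurements, correlation ρ = 0.5, α = 0.05.
- λ = N·f²·m / (1 + (m − 1)ρ) = 140 × 0.1885976² × 4 / 2.5 = 7.967
- Critical F(1, 138) = 3.910; power = 0.8004

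This reproduces the stated 140 (70 per group). The plan recruits 77 per group, which leaves 7 per group for drop-out.

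**4. Pregnancies (assumed inputs).** The documents give no number of women of child-bearing age and no pregnancy rate. Assume 46 to 77 women (about 30% to 50% of 154) and 3% to 8% per year, so 1.5% to 4% over six months.
- Low: 46 × 0.015 = 0.7
- High: 77 × 0.04 = 3.1

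That is about 1 to 3 participants, or 0.6% to 1.9% of 154, out of a total allowance of 2 × 7 = 14.

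**5. Effect on power (utility, same formula).**
- 154 complete: 0.837
- 153 complete: 0.834
- 151 complete: 0.830
- 138 complete (about 10% lost by all routes): 0.795

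Pregnancy losses alone cost less than one percentage point.

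**6. Effect on the estimate.** If a fraction q of an arm is lost and those lost differ from those retained by a gap g, the observed arm mean differs from the full-arm mean by q × g. Take every pregnancy loss in one arm of 77, the plan's pooled SD of 0.090139, and an assumed gap of 0.25 to 1.0 SD in the participant's average score.
- Low: (1/77) × 0.25 × 0.090139 = 0.0003, about 1% of the planned difference of 0.943 − 0.909 = 0.034
- High: (3/77) × 1.0 × 0.090139 = 0.0035, about 10%

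The sign is unknown. Equal losses with equal gaps in both arms would cancel. No comparable figure can be given for safety withdrawals, because the documents offer no basis for their number.

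**The case against.** The best defence is that the plan already limits the damage. Data from withdrawn participants stay in the analysis, reasons for withdrawal are documented, the enrolment log records randomization code and reason for early termination, and a 10% allowance exists for such losses. Pregnancy is also an exclusion criterion, so the investigators may not want outcomes measured during pregnancy to blur the comparison. All of this is fair and keeps the point small. It does not justify the rule. An intention-to-treat population is fixed at randomisation, and outcomes measured in pregnancy can be collected and flagged.

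A reader might infer more than the documents support:

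- **That the rules contradict the intention-to-treat analysis.** They do not. The plan includes all randomised patients and retains collected data. The defect is avoidable missing data.
- **That those with the worst outcomes are removed.** Worsening symptoms lead to an unscheduled visit, with ARIA grade and prescriptions recorded. Worsening is not a stated reason for withdrawal. The ethics section's trigger is risk from continuing participation, which the plan regards as minimal. For pregnancy, nothing indicates a direction.
- **That three days of unanswered calls end participation.** The rule is up to nine calls and, if necessary, a letter. It does not bar a person reached later from Day 120 or Day 180.
- **That withdrawn participants go unmonitored.** They are reminded to continue ENT care. What stops is study recording.

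**Conclusion.** The point holds in a narrow form. The pregnancy rule expressly ends outcome collection for a reason that does not require it, and the withdrawal rules never say whether assessment continues once counselling stops. Both undermine an analysis meant to cover every randomised patient.

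The size is probably small. Pregnancy alone is about 1 to 3 participants under the assumed number of women and annual rate. Power on utility would fall from 0.837 to no lower than about 0.830, and the shift in one arm's mean would be at most about 10% of the planned difference, with every loss in one arm and a 1 SD gap assumed. The number and direction of safety withdrawals and lost contacts are not in the documents, so a larger bias cannot be claimed. This is an inexpensive improvement and does not call the design into question.

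**What to change.** 1. In Ethical conduct of the study, Procedures in the event of Pregnancy, and Participant withdrawal & drop-out, state that a decision about counselling is separate from outcome collection. Whatever the clinicians decide about counselling, the scheduled Day 60, 120 and 180 outcome assessments and side-effect recording continue with the participant's consent. Only withdrawal of consent to follow-up ends data collection. Remove the reason based on the absence of an investigational product.
2. In Lost to follow up, state that a participant not reached at Day 60 or Day 120, after the calls and, if necessary, the letter, has a missed visit and is still contacted for later visits. Declare loss to follow-up only after the Day 180 window has closed.
3. Make the consent form match, so that participants can stop counselling and stay in follow-up.

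The cost is protocol and consent wording, a few contacts already in the schedule, and a flag for outcomes measured during pregnancy. The required sample size does not change. Whether counselling should stop in any of these situations is for the clinicians and is not judged here.

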## **Patient data protection**

The investigator will be responsible to assure that the participants' anonymity is maintained and that the confidentiality of records and documents that could identify participants will be protected, respecting the privacy and confidentiality rules in accordance with applicable regulatory requirements. Individuals involved in this study for medical care, qualified monitors and auditors, and governmental or regulatory authorities may inspect and copy the medical records, where appropriate and necessary. All participants will not be given access to their personal information and study data.

- The participants will be identified only by their assigned participants' identification number in all clinical report forms (CRF), study-related records and documents. There will be a Subject Identification List (Appendix B) with information on name,

contact number, address and hospital registration number with the corresponding study identification number. This Subject Identification List will be kept by the principle investigator on site in a locked-cabinet.

- All patients who are screened will be recorded in the Screening and Enrolment Log, which includes screen failures (Appendix C). This list will be kept separately in the study investigation file and separate from data collection sheet.
- Signed informed consent will be kept in a locked-cabinet, which can only be accessed by investigators on site.
- All data will be entered into and SPSS version 20.0 and the file will be password-protected. The electronic database only allows assigned investigators to enter and view data.

